## **18.Implementing personnel**

Trained pain management nurses act as program implementers, with the flexibility to adapt analgesic measures to the patient's specific situation. This approach aims to effectively control pain while reducing unnecessary medication use. Close monitoring and timely communication led by the nurse ensures that the pain management program is effectively implemented and adjusted based on patient feedback and physician guidance, thereby improving patient comfort and safety.

Observational indicators and measurements

## **19.Primary outcome measure**

Visual Assessment Scale-Pain (VAS-P): which consists of a 100-mm straight line, with one end indicating “no pain at all” and the other end indicating “the most severe pain imaginable”, with the patient marking the corresponding position on the line to represent his/her pain level. Patients marked the corresponding position on the line to represent their pain level. The data were collected by the data collectors at the specified time points (0h, 1h, 6h, 12h, 24h, 48h, 72h). Among them, 0h was before epidural placement, and the other times were 1h, 6h, 12h, 24h, 48h and 72h after epidural placement.

## **20.Secondary outcomes**

Intra-abdominal pressure (IAP): Measured by trans cystic intra-abdominal pressure measurement method. Specific operation is: the patient lying position, after indwelling catheter connected to the tee and pressure measuring tube, after draining the urine clamped closed urinary catheter, through the urinary catheter into the bladder 25 °C ~ 35 °C 25 ml of sterile saline, measuring tape aligned with the iliac crest axillary midline as the zero adjustment, when the liquid plane in the pressure measuring tube is no longer falling, in the end of the patient's exhalation, the scale number of the concave surface of the liquid surface in the pressure measuring tube to the scale number of the pressure is the intra-abdominal pressure. Measurement time and personnel are the same as the VAS-P.

Number of additional interventions (NAI): the number of additional interventions given by the pain management bedside nurses to patients with VAS-P greater than 3 or intolerable pain after continuous TEA in the control group and experimental group. The total number of interventions was recorded on Day1, Day2, and Day3, respectively.

Dosage of combined drugs (DCD): the total amount of combined drugs (nalbuphine 40 mg + ropivacaine 225 mg + lidocaine 0.2 g + 0.9% saline 6 ml, totaling 50 ml) during epidural placement.

Number of days of epidural placement (NDEP): calculated by the data collection researcher from the start of insertion to the time of extubation.

## **21.Adverse Events**

Puncture-related AE : Healthcare workers observe and record the following 8 indicators during daily care and examination: spinal cord and nerve root injury, epidural hematoma, puncture site infection, total spinal anesthesia, headache after dural puncture, intradural infection, catheter blockage, catheter breakage and ectasia. The number of cases of AE was counted for the period of epidural placement.

Drug-related AE: Pain management nurses observed and recorded the following 8 indicators after the patient's medication: anaphylaxis, hypotension, nausea/vomiting, itching, tremor, sensory disturbances in the lower limbs, fever, decreased oxygen saturation, bradycardia or tachycardia. The statistical methods and times were the same as those for puncture-related AE.

22.Outcome Indicators

Puncture surgery rate (PSR): Calculate the ratio of the number of successful puncture cases to the total number of punctures, which was counted by the data collector.

Length of stay in ICU (ICU-LOS): when patients are transferred out of ICU, the total number of days of ICU stay is recorded.

28-day mortality rate (28D-MR): count the number of patients who died within 28 days and calculate the 28-day mortality rate.

Satisfaction with analgesic effect (SAE): patients' satisfaction with the analgesic effect was assessed using a 0-10 scale, with 0 indicating very dissatisfied and 10 indicating very satisfied. It was collected by the data collector on the day of epidural tube removal.The intervention and data collection process are shown in [Figure 4](#).

[figure not shown]

Figure 5: Intervention and Data Collection Process

23. Quality control

(1) All staff must undergo standardized training and pass assessments to ensure consistent implementation of the intervention, minimizing both executor and assessor bias.

(2) Collected data will be cross-verified by two researchers before being entered into the system to ensure data accuracy.

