The etiology of AP, such as secondary to gallstones (the most common cause), alcohol, endoscopic retrograde cholangiopancreatography (ERCP), and various drugs, leads to pathological cell pathways and organelle dysfunction, ultimately causing acinar cell death and triggering local and systemic inflammatory responses. The pathogenesis of AP has not been fully elucidated, and currently, the trypsinogen theory is dominant in the development of SAP. This theory posits that various etiologies lead to the activation of trypsinogen, which in turn activates a series of digestive enzymes, resulting in autodigestion and damage to the pancreas. A large number of proteolytic enzymes trigger local inflammation in the gland, and the pancreas continuously releases pro-inflammatory cytokines such as interleukin IL-1, IL-6, and IL-8, and TNF- $\alpha$ , inducing a systemic inflammatory state. This subsequently leads to strong activation of the sympathetic nervous system, causing a reduction in blood flow to the gastrointestinal system, which in turn leads to pancreatic ischemic necrosis, systemic inflammatory response syndrome (SIRS), multiple organ dysfunction syndrome (MODS), and acute respiratory distress syndrome (ARDS), pleural effusion, hypovolemia, renal failure, and even death. Although the mortality rate of acute pancreatitis has decreased in recent years due to improved diagnostic and nursing levels, the incidence and long-term sequelae remain a significant challenge for clinicians.

Persistent upper abdominal pain and pain radiating to the back are the earliest and most common symptoms of AP. Adequate pain management is crucial for SAP management. The pain in SAP patients can progress from an initial 1-3 days of persistent vague pain to severe abdominal pain lasting for several days or weeks. If pain is not

controlled in a timely and effective manner, it will affect the patient's comfort and recovery progress, and may even impact the patient's mood. The use of intravenous opioids for pain relief is associated with corresponding persistent side effects, such as respiratory depression, somnolence, delirium, myoclonus, nausea, vomiting, constipation, immune suppression, endocrine disorders, and addiction, among many other adverse reactions.

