## **6. Research Content**

This study was a single-center, randomized, controlled clinical trial protocol planned to include 76 patients with SAP who were randomly divided into two groups in order to assess the efficacy and safety of different SMT-based nurse-led epidural analgesia delivery modalities. In the control group, continuous TEA was used with a combination of nalbuphine 40 mg, ropivacaine 225 mg, lidocaine 0.2 g, and 0.9% saline 6 ml in a total of 50 ml, which was pumped at a rapid duration of 3-5 ml/h. When the patient's VAS-P exceeded 3 points or when the patient was unable to tolerate pain, the pumping of the combined solution was appropriately adjusted upward by 1-2 ml/h. In the experimental group, on the basis of continuous TEA, a pain management nurse led the TEA pain management strategy according to the SMT, reported to the doctor when the VAS-P exceeded 3 points or when the patient was unable to tolerate pain, and injected 5 ml of the combined drug solution intermittently with an intermittent interval time of greater than 2 hours each time, as per the doctor's prescription. Hours. The patient's pain response and feedback were also continuously monitored for timely adjustment of analgesic measures. The primary outcome indicator was VAS-P, and secondary outcome indicators included intra-abdominal pressure(IAP), number of additional interventions(NAI), dosage of combined drugs(DCD) , number of days of epidural placement(NDEP), and 16 adverse events(AE). Outcome indicators included puncture success rate(PSR), length of stay in ICU (ICU-LOS), 28-day mortality rate (28D-MR), and patient satisfaction score for analgesic effect(SAE).

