### **17.Study interventions**

Control group: Continuous TEA using a drug combination of: nalbuphine 40 mg + ropivacaine 225 mg + lidocaine 0.2 g + 0.9% saline 6 ml in a total volume of 50 ml at an infusion rate of 3-5 ml/h. When the patient's VAS-P exceeded a score of 3 or the pain was intolerable, upward adjustment of the pumped medication was made by 1-2 ml/h. and the number of additional interventions was recorded.

Experimental group : On the basis of continuous TEA, the pain management nurse led the TEA management strategy based on STM, and when the patient's VAS-P exceeded a score of 3 or pain was intolerable, an epidural injection of 5 ml of the combined drug solution was immediately administered, and the number of additional interventions was recorded. The duration of each interval was greater than 2 hours, and the patient's pain response and feedback were continuously monitored so that analgesic measures could be adjusted in a timely manner.

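### Drug-related adverse events are assigned by timing alone, so signs of pancreatitis already present before placement dilute the safety comparison; some opioid effects lie outside it, and the stated count of events does not match the list

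*Protocol*

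**What the plan says.** Section 21 has two lists. The drug-related one opens with "Pain management nurses observed and recorded the following 8 indicators after the patient's medication: anaphylaxis, hypotension, nausea/vomiting, itching, tremor" and continues with "sensory disturbances in the lower limbs, fever, decreased oxygen saturation, bradycardia or tachycardia". For the window, the puncture-related paragraph says "The number of cases of AE was counted for the period of epidural placement", and the drug-related paragraph adopts the same methods and times. Section 21 gives no threshold, no comparison with the state before placement and no causality step.

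The background section (part I) describes the disease as leading to "systemic inflammatory response syndrome (SIRS), multiple organ dysfunction syndrome (MODS), and acute respiratory distress syndrome (ARDS), pleural effusion, hypovolemia, renal failure". It also calls paralytic ileus a common complication, and lists harms of intravenous opioids that include "respiratory depression, somnolence, delirium, myoclonus, nausea, vomiting, constipation".

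Section 16 names pain score and intra-abdominal pressure as the measurements taken before placement. APACHE-II, CTSI, Ranson and related complications are also baseline items, but none is linked to event counting.

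Section 7, hypothesis 2, expects adverse event incidence in the experimental group to be no higher than in the control group and states no margin. Section 24 compares event frequencies by chi-square or Fisher's exact test. Section 6 gives the total as "and 16 adverse events(AE").

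**The concern.** The label says drug-related, but the rule behind it is only that the sign was seen after medication while the catheter was in place. A patient who is febrile and tachycardic at 0h, which section 19 places before epidural placement, meets the rule as soon as the drug has started. That can happen in either arm whatever the drug does.

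The safety hypothesis is one of no excess. Events that have nothing to do with treatment add similar numbers to both arms, pull the two proportions together and make a non-significant result more likely. Here such a result is the one the trial hopes for. A loose definition therefore works in favour of the claim being tested.

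Two smaller points sit in the same section. The infused solution contains nalbuphine, yet several opioid effects that the protocol itself names are missing from the compared events. And the number of events announced does not match the number listed.

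**Working it through.** **1. The plan's own counts.** Puncture-related list, as punctuated: cord and nerve root injury; epidural hematoma; site infection; total spinal anesthesia; post-puncture headache; intradural infection; catheter blockage; breakage and ectasia. That is 8, as stated. Drug-related list: anaphylaxis; hypotension; nausea/vomiting; itching; tremor; lower-limb sensory disturbance; fever; desaturation; brady- or tachycardia. That is 9, against a stated 8. The total is 8 + 9 = 17, against 16 in section 6.

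**2. Overlap with the disease.** Five of the nine drug-related entries can come from conditions that part I attributes to pancreatitis: fever and tachycardia (SIRS), desaturation (ARDS, pleural effusion), hypotension (hypovolemia) and nausea/vomiting (ileus). Anaphylaxis, itching, tremor and lower-limb sensory disturbance are much less exposed.

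**3. Size of the dilution.** The protocol gives no adverse event rates and no sample size for this comparison. Its 76 patients (38 per arm) were set for VAS-P. The following is therefore an illustration.

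Inputs: n = 38 per arm (76/2, section 12); two-sided 0.05 and Fisher's test (section 24). Assumed: drug-caused risk d of 10% in control and 40% in experimental; a background b of disease-caused signs, equal in both arms and independent of the drug; the endpoint is any listed sign.

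Observed risk: p = b + (1 − b)d. The difference between arms is (1 − b) × (0.40 − 0.10), so it shrinks in proportion to 1 − b. Example at b = 50%: control 0.50 + 0.50 × 0.10 = 0.55; experimental 0.50 + 0.50 × 0.40 = 0.70.

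| Background b | Control | Experimental | Difference | Ratio | Exact Fisher power |
|---|---|---|---|---|---|
| 0% | 10% | 40% | 30 points | 4.00 | 83% |
| 20% | 28% | 52% | 24 points | 1.86 | 48% |
| 50% | 55% | 70% | 15 points | 1.27 | 20% |
| 80% | 82% | 88% | 6 points | 1.07 | 6% |

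Sensitivity: with 10% against 30%, power is 50% at no background, 23% at 20%, 13% at 40%, 8% at 60% and 4% at 80%. With 33 completers per arm and 10% against 40%, it is 75% at no background and 5% at 80%.

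**4. Opioid effects.** Set against the part I list, nausea and vomiting are in section 21. Desaturation partly stands in for respiratory depression, and tremor partly for myoclonus. Somnolence and delirium have no counterpart. Constipation has none either, but ileus makes it another sign that the disease can cause, so adding it would bring back the problem in step 2.

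**The case against.** **The analysis plan may define treatment-emergent events.** It may, and missing detail alone would be no finding. But section 21 itself fixes the label, the trigger and the window. A later analysis rule would still need the 0h state of each sign, which section 16 does not tie to event counting.

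**The rates are assumed and the composite is not in the protocol.** Both are true. Section 21 lists indicators and counts cases, and does not define an any-event endpoint. Compared one by one, the four less exposed indicators are little affected. Section 11 excludes severe organ failure and serious infection, and section 10 limits the population to awake patients, which lowers the background at entry. At 10% against 30%, power is only 50% with no background, so part of the weakness is sample size.

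**Observation may be unequal.** A reader might infer that closer watching after each injection biases the count against the experimental arm, since section 17 says there that "the patient's pain response and feedback were continuously monitored". The documents do not support this. That sentence concerns pain and feedback. Section 21 sets one period for all events, and sections 29 and 32 promise monitoring without distinction of arm. Control patients also have discrete rate increases, and under a continuous infusion all later time is after medication.

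**Opioid effects can be recorded.** A reader might infer that non-serious sedation or delirium can never be captured. That is too strong: sections 9, 32 and 34 have adverse reactions recorded in general terms, and section 25 collects all serious events. Part I also names these harms for intravenous opioids, not for the epidural mixture. What stands is that they are outside the pre-named comparison.

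**Conclusion.** The point holds as one of dilution and incomplete coverage. Section 21 counts signs that the disease can cause as drug events, including signs already present at 0h. Randomisation balances that background on average, so the consequence is a smaller observed difference and lost power, not bias between arms. The direction is the same at any background rate and favours the no-excess hypothesis.

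The size is unknown. It could be modest or could remove nearly all power, depending on the background rate and on whether events are analysed together or singly. A reader might conclude that the safety comparison is swamped by disease; without event rates in the protocol, that cannot be shown.

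The background in the illustration covers all disease-caused signs during placement. A comparison with 0h removes only those already present, so it recovers part of the loss; disease signs that start later remain in both arms.

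The absence of somnolence, delirium and respiratory depression from the compared events is a real but narrower gap. The mismatches of 8 with 9 and 16 with 17 are certain; they need correcting so that it is clear which entries form the outcome.

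**What to change.** Amend section 21 as follows.

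- Record each listed sign at 0h, taken from routine ICU charting, and add these items to the baseline data in section 16.
- Count a sign as an event only if it is new or worse than at 0h, by definitions fixed in advance and applied on the same observation schedule in both arms.
- Add somnolence, delirium and respiratory depression to the events compared between groups.
- Reconcile the 8 in section 21 and the 16 in section 6 with the final list.

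The cost is amendment wording, a few more data fields and a few more event types to tabulate. Event counts will differ from those under the present rule. If patients have already been enrolled, their 0h signs would have to be taken from the charts. No treatment rule changes.

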Thoracic epidural anesthesia (TEA) involves intermittent injection of low-concentration local anesthetics through a catheter into the epidural space, surrounding the connective tissue around the nerve roots, and blocking the regional nerve roots through local infiltration. It is a minimally invasive treatment method that reversibly controls the activity of sympathetic nerves within the region. TEA is a widely used anesthetic technique that can produce extensive visceral sympathetic and sensory nerve block effects, with roles in pain relief, anti-inflammation, and vasodilation to improve visceral organ perfusion. In addition to providing good anesthesia and analgesia, TEA also has many non-analgesic effects. Studies have shown that intraoperative and postoperative local application of anesthetics in the epidural space can prevent a reduction in visceral microvascular perfusion and shorten the recovery time of gastrointestinal function. In animal experiments conducted by Wang X et al., it was found that thoracic epidural anesthesia significantly promotes distal gastric microcirculatory perfusion and enhances the vitality of the stomach and intestines. Wang Huiying's research indicated that TEA can reduce the impact on gastrointestinal perfusion during endotoxemia while ensuring hemodynamic stability. It was also found that thoracic epidural anesthesia promotes gastric mucosal blood flow during sepsis. Paralytic ileus is a common complication of acute pancreatitis, and thoracic epidural anesthesia can improve paralytic ileus by blocking nociceptive afferent nerves and thoracolumbar sympathetic efferent fibers to maintain the function of parasympathetic efferent fibers. In addition to its analgesic effects, the regulatory role of TEA can also improve organ perfusion, delay intestinal acidosis in hypoxia, increase intramucosal pH in patients with peritonitis, thereby reducing postoperative complications, shortening hospital stay, and improving survival rates.

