#### **24.Data analysis**

Data will be analyzed in this study using GraphPad Prism software to ensure accuracy and consistency of results. For baseline characteristics data, patients' age, gender, admission time, and disease-related clinical information will be descriptive statistics, Categorical variables will be presented as frequencies and proportions, whereas normally distributed continuous variables will be described using means and standard deviations. For non-normally distributed data, descriptive statistics will utilize median and percentile values (P25 and P75). Between-group comparisons will be carried out using t-tests, analysis of variance, chi-square tests, Mann-Whitney U tests, and statistical methods for repeated measures data to assess differences among the groups. The significance level in this study will be set at  $\alpha=0.05$ , with  $P<0.05$  indicating statistical significance.

The changes in the primary outcome indicator VAS-P at different time points (0h, 1h, 6h, 12h, 24h, 48h, 72h) will be assessed by repeated measures analysis of variance (ANOVA) if the data conform to a normal distribution. Secondary outcome indicators, such as intra-abdominal pressure (IAP), will be analyzed in the same manner. The number of additional interventions (NAI) and the dose of coadministered medication (DCD) will be expressed as mean  $\pm$  SD or median (IQR), and comparisons between groups will be made using the t-test or the Mann-Whitney test. The number of days of epidural placement (NDEP) will also be subjected to descriptive statistics and between-group comparisons. The number of cases of adverse events (AE) will be expressed as frequency, and comparisons between groups will be made using the chi-square test or Fisher's exact test. The outcome indicators, including puncture success rate (PSR), length of stay in the ICU (ICU-LOS), 28-day mortality rate (28D-MR), and satisfaction with analgesic effect score (SAE), will be subjected to descriptive statistics and between-group comparisons using the chi-square test or Fisher's exact test, as well as the t-test or the Mann-Whitney test.

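### Section 21 counts bradycardia and tachycardia as one adverse-event indicator, which can dilute or hide a between-arm difference in either, and its stated total of 8 does not match the 9 entries listed

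*Protocol*

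**What the plan says.** Protocol section 21 sets out two lists. The puncture-related list is introduced by "Healthcare workers observe and record the following 8 indicators during daily care and examination" and the drug-related list by "Pain management nurses observed and recorded the following 8 indicators after the patient's medication". The drug-related list closes with "sensory disturbances in the lower limbs, fever, decreased oxygen saturation, bradycardia or tachycardia". No separate count is given for the two heart-rate events. Cases are counted over the time the epidural catheter is in place.

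Section 6 gives the overall number of indicators as "16 adverse events(AE". On analysis, section 24 says "The number of cases of adverse events (AE) will be expressed as frequency". It then provides for a chi-square comparison of the arms, with Fisher's test as the alternative. It does not say whether this is done for each indicator or overall.

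Section 7, hypothesis 2, expects adverse-event incidence to be no higher in the experimental arm and takes that, with ICU stay and 28-day mortality, as a sign that the method is safe.

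**The concern.** A slow and a fast heart rate are departures in opposite directions. A count that treats them as one event cannot show which of them differs between the arms. If one is common and similar in both arms, it adds noise and dilutes a difference in the other. If one rises while the other falls, the combined count can be equal in the two arms when neither component is.

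The indicator is among those from which hypothesis 2 would be judged, so a blunted or cancelled comparison would support a finding of no excess harm that the data do not justify. The problem also starts at recording. If the case form carries one combined item, no later analysis can separate the events.

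The stated number of indicators does not match the list either, so whoever builds the form or the adverse-event table cannot tell from the text which items are meant.

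**Working it through.** **1. The stated counts.** Puncture-related entries, taking each item between commas as one: cord or root injury; epidural haematoma; infection at the site; total spinal; post-puncture headache; intradural infection; blocked catheter; catheter breakage with ectasia. That is 8, as stated.

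Drug-related entries counted the same way: anaphylaxis; low blood pressure; nausea or vomiting; itch; tremor; altered leg sensation; fever; desaturation; the heart-rate entry. That is 9, not 8. With the heart-rate entry split it is 10. The total is 8 + 9 = 17 as listed, or 8 + 10 = 18 after the split, and not 16 on either reading.

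**2. One entry or two?** The puncture-related list reaches its stated 8 only when each item between commas counts once, including a paired last item. By the same rule the heart-rate pair is one indicator. That reading is also nearer to the stated 8 (9 rather than 10).

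**3. What a combined count can do.** Inputs from the protocol: 76 patients allocated 1:1, so 76 / 2 = 38 per arm (section 12), and a 0.05 significance level with a chi-square or Fisher test (section 24). The event rates are assumed, because the protocol gives none.

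Example with assumed counts out of 38 (control v experimental, each patient in one category):
- Bradycardia 1 v 9: Fisher p = 0.014.
- Tachycardia 12 v 4: p = 0.047. Pooled 13 v 13: p = 1.00.
- If tachycardia is instead 12 v 12, pooled 13 v 21: p = 0.106.

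**4. Power.** With n = 38 per arm, power = Σᵢ Σⱼ Bin(i; n, p₀) × Bin(j; n, p₁) × 1{two-sided Fisher p < 0.05}. Assumed control rates are bradycardia 5% and tachycardia 40%, so pooled 5 + 40 = 45%.

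| Experimental arm (assumed) | Pooled rates | Bradycardia alone | Pooled |
|---|---|---|---|
| Bradycardia 30%, tachycardia 40% | 45% v 30 + 40 = 70% | 79% | 51% |
| Bradycardia 30%, tachycardia 15% | 45% v 30 + 15 = 45% | 79% | 3% |
| Bradycardia 20%, tachycardia 40% | 45% v 20 + 40 = 60% | 38% | 19% |
| Bradycardia 20%, tachycardia 25% | 45% v 20 + 25 = 45% | 38% | 3% |

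The 3% rows are set to cancel exactly, so 3% is simply the rejection rate of a Fisher test when the two pooled rates are equal. They mark the extreme. The rows with tachycardia unchanged show dilution alone.

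**5. Sensitivity.** With 33 per arm (section 12 before the dropout allowance), bradycardia alone has 70% and 29% power in place of 79% and 38%.

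If a patient can have both events, independently, the pooled rate is 1 − (1 − b)(1 − t). With tachycardia at 40% in both arms, control is 1 − 0.95 × 0.60 = 43%. The experimental arm is 1 − 0.70 × 0.60 = 58%, or 1 − 0.80 × 0.60 = 52%. At 38 per arm, pooled power is then 19% or 8%, so dilution is greater when events overlap.

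**The case against.** **A combined analysis is inferred.** The word joining the two events may simply close the list, section 24 does not say whether indicators are tested singly, and tabulation of adverse events is commonly left to the statistical analysis plan, which is not at hand. This stands in part: the text does not state a pooled test. But section 21 itself fixes what is recorded, and its most natural reading is one item. If two were intended, the same edit is needed.

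**The mechanism.** A reader might infer that, on the protocol's own account, pancreatitis drives heart rate up and epidural block drives it down, so that the arms must differ in opposite directions. The background does say of the disease "This subsequently leads to strong activation of the sympathetic nervous system", and of epidural anaesthesia "It is a minimally invasive treatment method that reversibly controls the activity of sympathetic nerves within the region". Neither statement mentions heart rate. Both arms have the disease and both receive continuous epidural infusion (section 17), so this opposition does not separate them.

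Nor does the protocol show more block in the experimental arm. Control patients are escalated too, by 1-2 ml/h. If one such increase were held for 24 hours (an assumption), it would add 24-48 ml, against 5 ml per injection. Total dose is an outcome with no predicted direction (section 20). This objection stands: cancellation is possible, not predicted.

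**Power figures.** The 3% results come from rates chosen to cancel. This also stands, and is why the unchanged-tachycardia rows are shown beside them. If both events moved the same way, pooling could even help, but a combined count can always be derived from separate records and the reverse is impossible.

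**The miscount.** It may be a slip and does not prove that items were meant to be merged. Agreed. It still needs correcting.

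**Conclusion.** The point holds in a limited form. As written, two opposite events share one indicator, and a between-arm count on it can dilute a difference in either, or hide it if they move in opposite directions. Under the assumed rates, power to see a bradycardia excess falls from 79% to 51%, or from 38% to 19%, when tachycardia is the same in both arms, and to about 3% only with exact cancellation. These figures rest on assumed rates, on 38 per arm, on each patient counting once, and on reading the entry as one item. They are illustrations, not forecasts.

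The documents do not support saying that the plan will misreport the cardiac effect, or that the experimental arm will have more bradycardia. Nor do they support keeping tachycardia out of the safety judgement, since section 21 lists it as a drug-related event.

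The count error needs no assumption: 8 is stated and 9 are listed, so 16 is wrong as well. The primary outcome is unaffected. What is at risk is the clarity of one safety comparison that feeds hypothesis 2.

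**What to change.** In section 21, replace the joint heart-rate entry with two indicators, bradycardia and tachycardia. Record each separately on the case form and report each by arm. Correct the stated number of drug-related indicators to 10, and the total in section 6 to 18. If the sponsor keeps the joint entry, the counts should read 9 and 17, and the protocol should say that the two events are deliberately combined.

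The cost is one line in section 21, two corrected figures and one more row in the adverse-event table. Both events are already to be observed, so no new assessment is needed. The downside is one additional comparison.
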